#### Intervention group

Visit 1: The dietary interview will consist of a comprehensive nutritional assessment followed by the GFD education. “Your Guide to Well-being: Managing Celiac Disease and Diabetes” is a resource manual, divided into modules, that was specifically designed for this population to address the complex dietary nature of living with both CD and T1D. This resource as well as "Pocket Dictionary of Ingredients" and 'Checking Ingredient List' by the Canadian Celiac Association will be provided to the participants along with the GFD education. Participants will be directed to online resources such as Apps that will help and guide them in determining presence of gluten in food, as well as locations of gluten free restaurants and stores in their vicinity. At the end of the education session an assessment will be carried out using food labels for the comprehension of the GFD, carb counting skills and current diabetes management. Three day food records will be collected, clarified and sent to central analysis for ESHA (Elizabeth Stewart Hands and Associates) processing.

#### Control group

Visit 1: The dietary interview will consist of a comprehensive nutritional assessment including on how well the subjects are managing their current diet and ensuring consumption of GC foods. Food labels will be used to assess carbohydrate counting skills. Three day food records will be collected, clarified and sent to central analysis for ESHA processing.

A 4 week follow-up call will be done in both groups to support, address questions and concerns, document any changes in non-insulin medications, supplements and vitamins and document adverse events including severe hypoglycemia requiring assistance.

### Follow-up visits 2, 3 and 4 (Months 3, 6 and 9)

#### Intervention group

The dietary interview will address any gaps in education; provide nutritional support and reinforcement of GFD topics and modules, as required. Subject's food records analysis from visit 1 will be reviewed for imbalances and deficiencies in macronutrients as per Canadian Diabetes Association guidelines and against DRIs. A plan to address any issues or concerns will be implemented and a “Typical Day Intake” will be performed to assess for gluten exclusion and/or inclusion. Subjects with the dietitian will complete a 'self-report' questionnaire designed to assess their comfort with their assigned diet. The dietitian will rank the subjects adherence using specific criteria, see Fig 3. Three day food records will be provided for visit 3.

#### Control group

The dietitian interview will aim to support current dietary management. Subject's food records analysis from visit 1 will be reviewed for imbalances and deficiencies; a plan to address any issues or concerns will be implemented. A “Typical Day Intake” will be performed to assess for gluten exclusion and/or inclusion. Subjects with the dietitian will complete a 'self-report' questionnaire designed to assess their comfort with their assigned diet. The dietitian will rank the subjects adherence using specific criteria, see Fig 3. Three day food records will be provided for visit 3.

At 3 (Visit 2) and 9 months (Visit 4) a “Typical Day Intake” interview will be performed as part of the diet interview and food records will be provided for next visit. At visit 3 and 5 (6 and 12 months) in addition to the dietary interview, food records will be collected and sent to central analysis for ESHA processing. Handouts specific to each group (GFD/GCD) have been designed to address the possible dietary deficiencies or imbalances in macronutrients as well as fiber, iron, calcium and vitamin D.

### Conditional telephone contact (Month 7)

This telephone call will apply to subjects who are found to be non-adherent (as per TTG IgA results from Visit 3) to their assigned diet. For both groups: dietitian will address follow-up questions and concerns, barriers to dietary adherence, document any changes in insulin regimen or in non-insulin medications, supplements and vitamins, document adverse events including severe hypoglycemia requiring assistance.

### Visit 5 (Month 12)

For both arms this visit will entail all of the details as per visit 3 (month 6) visit. The dietitian will conduct an exit interview consisting of 7 questions for GFD and 4 questions for the GCD. Subjects assigned to the GCD will be asked if they would like to follow the GFD.

### Outcome assessments

#### CDAT and TTG and Dietitian’s ranking

We anticipate that the subjective ranking by the dietitian will correlate with the subject’s TTG, CDAT and self-report in both arms. We also anticipate that the average GI and the GL content of the GFD will be higher than the GCD due to the nature of some of the GF foods which tend to be more refined higher in carbohydrate and contain less fiber than the GC equivalents. The difference in GI and GL between the groups may also explain the possible BG variability in both groups as will be documented with (continuous glucose monitoring (CGM)).

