**Fig. 3 Fig3:**
[figure not shown]
methods of Assessment for GFD/GCD arms

A 3 day food record will be collected and clarified. Subsequently, records will be sent to central analysis where nutrient intake will be analyzed using the computer based ESHA food processor which contains a wide data base capable of analyzing over 160 food nutrient components and compare to DRIs. The analysis will include macronutrient distribution to be compared to CDA practice guidelines and specific nutrients including calcium, iron, vitamin D and fiber. Alterations in macronutrients, vitamins and minerals have been associated with imbalances and/or deficiencies with the GFD [5–8]. Additionally, Glycemic index (GI) and glycemic load (GL) of mixed meal will be calculated and analyzed for both GFD and GCD.

In this study we are also planning to describe the food consumption patterns of our population with dietary gluten. This will be done by multiplying the plant proteins of overt gluten sources by a factor of 0.8 [29]. This is a relatively novel approach in North America in relation to its application to dietary intake. Our findings from a previous study show that this approach to dietary gluten estimation is reasonable and valid (29). Dietary gluten for the GFD group will be estimated by using the maximum 20 ppm standard as defined by Health Canada’s labelling regulations [30].2.Celiac dietary Adherence Test (CDAT)- a 7 item questionnaire that has been demonstrated to have a highly predictive value (88 %) for verifying compliance with the GFD in adults, as compared to TTG IgA and dietary evaluation [31]. It will be administered to the subjects randomized to the GFD at every visit after randomization (visits 2–5) (Fig. 4).

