### Dietitian visits

All subjects on both arms of the study will have five visits with a trained dietitian. Worksheets specific to each arm and visit have been designed to ensure consistent collection of information, and uniform parameters for assessment and education. All worksheets will be filled out by the dietitian at every visit. All participants will fill out food records (two weekdays and 1 weekend day) for visits 1, 3 and 5 (at initial assessment, 6 month and 12 months). Food records will be sent to ESHA, and will be reviewed with the participants at their following visit (visits 2 and 4, 3 and 9 months, respectively). Glycemic Index (GI) and Glycemic load (GL) will be calculated to describe the dietary carbohydrates of each arm using glucose as a reference. GI of mixed meals per day will be ranked as: Low GI ≤55, Medium GI 56–69 and High GI ≥70. Similarly GL per day will be ranked as: Low GL <80, Medium GL 80–120 and a high GL >120 [32]. Dietary gluten evaluation will be performed by using the Osborne formula for all subjects at baseline. Twenty ppm will be applied to the GFD arm as per Health Canada’s definition of GF claims.

A typical day intake is incorporated into the dietary interview at visits 2 and 4 (3 and 9 month visit respectively). All records will be assessed for dietary exclusion or inclusion of gluten. At visits 2–5 (3,6,9, and 12 months) inclusive all participants will complete with the dietitian a 'self-report' questionnaire designed to assess their comfort (both groups) and understanding of their assigned diet.

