### Dietary adherence

Dietary adherence will be assessed at each visit following the baseline visit. Adherence assessment will be classified as objective and subjective as described earlier.

Subjective and objective assessment of adherence will include food records collected at visits 1, 3 and 5 (randomization, 6 and 12 months) and a typical day intake at visits 2 and 4 (3 and 9 months) for both groups. All records will be evaluated for inclusion and exclusion of gluten. In addition, food records will be analyzed via ESHA, dietary food processor. GI/ GL and gluten content will be assessed at baseline, 6 and 12 months in both arms. For the intervention group, the adherence to GFD will be further assessed by the application of the Celiac Dietary Adherence Test (CDAT). Additionally, TTG-IgA titers will be measured at 6 (Visit 3) and 12 months (Visit 5) visits to asses GFD/GCD compliance.

After randomization (visit 1) at visits 2 to 5, both study groups, intervention and control, will be interviewed to assess and document adverse events including severe hypoglycemia requiring assistance, hospitalization, any changes in non-insulin medications, supplements and vitamins from previous visit. HbA1c and TTG will be collected at visits 1, 3 and 5 for both arms. GISS and CDAT questionnaires will also be completed only for intervention group, at each visit.

A trained dietitian from the leading site will train identified dietitians from the partner sites using standardized educational material and a detailed manual of operations describing the goals objectives of the dietary curriculum and the steps for the dietary interview at each visit. The standardized tools will be used to maintain quality and consistency of dietary education and collection of information.

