## Discussion and dissemination

The CD-DIET study is a large scale clinical trial that will further contribute to the pool of knowledge and novel implications to the treatment of asymptomatic celiac disease and TID. The dietary curriculum will be coordinated across all centers by the main site dietitian, using standardized educational materials and a manual of operations. Both pediatric and adult patients will be randomized to a GFD or GCD. Adherence to the diets will be determined from the dietary interview, TTG-IgA blood tests and CDAT (GFD) and subjects’ self-report. CDAT is highly correlated with Standardized Dietician Evaluation (SDE) and even superior to TTG IgA serology with regards to GFD adherence [31]. The Canadian context to the study is important, as the 2013 Canadian Diabetes Association’s clinical practice guidelines suggests a targeted symptom based screening approach [33]. While the literature supports the implementation of a GFD in symptomatic CD and T1D patients, it is less clear as to the benefits for asymptomatic patients. Our curriculum was established in concurrence with the current literature and is designed to address a number of issues: the limited educational literature the challenges associated with dietary quality and adherence and the implicated social challenges of a GF lifestyle in addition to T1D and. Participants will be supported by dietitians throughout the study and subjects on the intervention group and later the control group will have to have access to ‘Your Guide to Well-being: Managing Celiac disease and Diabetes' a resource specifically designed to address the nutritional intricacies and related challenges of both conditions: CD and T1D.

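### The expected correlation of ranking with CDAT has no data in controls, and the dietitian's ranking is not independent of the self-report

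*Protocol article*

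**What the plan says.** The subsection on CDAT, TTG and the dietitian's ranking, under Outcome assessments, anticipates that the ranking will correlate with "TTG, CDAT and self-report in both arms".

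The article describes the four measures as follows.

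- **CDAT.** Objective measures of assessment: "It will be administered to the subjects randomized to the GFD at every visit after randomization" (visits 2 to 5). Dietary adherence: "GISS and CDAT questionnaires will also be completed only for intervention group, at each visit". Discussion and dissemination ties it to the same arm when listing the adherence sources: "TTG-IgA blood tests and CDAT (GFD").
- **TTG.** Dietary adherence: "HbA1c and TTG will be collected at visits 1, 3 and 5 for both arms".
- **Self-report.** Dietitian visits: at visits 2 to 5 "all participants will complete with the dietitian a 'self-report' questionnaire". Discussion and dissemination makes clear that this questionnaire carries the strict, partial or non-adherent rating.
- **Dietitian's ranking.** Subjective measures of assessment has the dietitian apply it when each dietary interview closes. The GFD arm is ranked on a scale of expectations, and the gluten-containing diet (GCD) arm on a scale of gluten inclusion or restriction.

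The month 7 telephone contact, made by the dietitian, applies in both groups to participants "found to be non-adherent (as per TTG IgA results from Visit 3").

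**The concern.** Two things in the stated expectation do not fit the stated procedures.

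First, it claims a correlation with CDAT in both arms, although controls never complete CDAT.

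Second, it treats the ranking and the self-report as two measures whose agreement is informative, although the person giving the ranking also takes part in filling in the self-report. A high correlation between them could then reflect the shared conversation as much as the participant's diet.

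The article gives this agreement some weight. Discussion and dissemination acknowledges that patients tend to overstate adherence and that self-reports become less reliable with time on the diet, and it sets against this a close correlation found earlier between self-reports and dietitians' assessments. A further correlation obtained jointly would not answer that doubt. Adherence data will also be needed to interpret whatever effect of the diet is found.

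**Working it through.** There is no sample size, power or alpha figure to reproduce. The check is a count of which ranking-versus-measure pairs will have data, followed by a reading of how each measure is obtained.

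**Step 1: pairs implied by the expectation.** Three comparators × two arms = 6 pairings.

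| Ranking against | Follow-up visits with data, GFD arm | Follow-up visits with data, GCD arm |
|---|---|---|
| Self-report | 4 (visits 2 to 5) | 4 (visits 2 to 5) |
| TTG | 2 (visits 3 and 5) | 2 (visits 3 and 5) |
| CDAT | 4 (visits 2 to 5) | 0 |

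- Pairings with data: 5 of 6. The empty one is CDAT in controls.
- Arm-visit pairs implied if CDAT were given in both arms: self-report 4 × 2 = 8, TTG 2 × 2 = 4, CDAT 4 × 2 = 8, total 20.
- Arm-visit pairs with data: 8 + 4 + 4 = 16. The 4 missing are all CDAT in controls.

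**Step 2: independence of ranking and self-report.** Dietitian visits, and the intervention and control paragraphs for visits 2 to 4, have the questionnaire completed together with the dietitian. The paragraphs for visits 2 to 4 describe the ranking directly afterwards, and Subjective measures of assessment places it at the close of the interview. So in all 8 ranking/self-report arm-visit pairs the rater has taken part in producing the comparator. Reversing the order would not remove the link: a dietitian who has already formed a view would still be helping with the form.

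**Step 3: independence of ranking and TTG.** TTG is a laboratory assay, and nothing in the article shows that a same-visit result is known when the ranking is made. The only route by which TTG can reach the ranking is the month 7 call.

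- Visit 3: the ranking precedes any call. This is the clean pair.
- Visit 4: no TTG is drawn, so there is no same-visit pair.
- Visit 5: for participants called at month 7, the ranking may be coloured by the visit 3 result, and it is then compared with the visit 5 assay.

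**Step 4: scale and direction.** The two arms use different ranking scales. Objective measures of assessment expects TTG to normalise or fall with adherence on the GFD and to stay raised on the GCD. A correlation between ranking and TTG therefore has a meaning only within an arm.

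**The case against.** The best reply is that the CDAT wording is a slip: three other places settle who completes CDAT, so no careful reader would expect control data. The expectation is also only something the authors anticipate. It is not called a validation, an endpoint or a hypothesis test, and the statistics paragraph does not include it. The order of forms and any masking of the dietitian may be set out in the visit worksheets or the manual of operations, which are not shown.

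Much of this stands, and it keeps the point small. It does not remove it. The article does state that the self-report is completed with the dietitian, and that procedure by itself creates the dependence.

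A reader might infer more than the text supports:

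- *That the whole expectation cannot be tested.* Five of six pairings have data. Non-independence may inflate a correlation, but it does not prevent computing it.
- *That later rankings are generally made with knowledge of TTG.* The article describes a call only to those flagged at visit 3. It does not say that the caller is also the ranker or that dietitians see TTG values. The exposure is at most an earlier flag in a subset of unstated size, and it matters for one TTG time point, visit 5.
- *That the arms will be pooled, mixing opposite signs.* No section pools them. The different scales argue against it, and the TTG direction is already given per arm.
- *That CDAT's accuracy is overclaimed for children.* The article itself limits the evidence to "verifying compliance with the GFD in adults, as compared to TTG IgA and dietary evaluation" and claims none for children.

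**Conclusion.** The point holds in limited form. The CDAT part of the expectation contradicts the rest of the article and has no data in controls: 1 of 6 pairings, 4 of 20 arm-visit pairs. The agreement between ranking and self-report is not independent at any of the four follow-up visits in either arm and is likely too high. The article gives no figures from which to calculate by how much. The ranking can still be set against TTG in both arms and against CDAT in the GFD arm, with visit 3 the cleaner time point for TTG.

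This rests on two assumptions: that the dietitian who helps with the self-report is the one who ranks, which is the plain reading of the visit descriptions; and, for the visit 5 caution only, that the month 7 caller, or what that caller learned, reaches the ranker.

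To conclude that the trial will claim a validity it has not shown would be speculation. This is a descriptive adherence outcome of minor weight. The primary HbA1c analysis is untouched.

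**What to change.** 1. Reword the expectation so that CDAT is named for the GFD arm only.
2. Have the participant, with a parent for a younger child, complete the self-report without the dietitian, and keep it unseen until the ranking has been entered. If that cannot be arranged, report the ranking/self-report agreement as non-independent.
3. Analyse ranking against TTG within arm. Treat visit 3 as the cleaner time point, and note at visit 5 that the rankings of participants called at month 7 may reflect the earlier flag. The call itself need not change.

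The cost is a small change in the order of the visit, some parental help for younger children, and a few words in the analysis description. No extra measurement is needed.

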### Changes in dietary intervention assignment (cross-overs)

In cases of symptom presentation as defined by Mahmud et al. [28] subjects will be crossed over into the GFD.

Power calculation and statistics:

The outcome measure used to calculate sample size will be the change in HbA1c level from baseline to month 12. Based on previous work, in a non-randomized comparison of HbA1c levels over time in type 1 diabetes patients with asymptomatic CD who received a GFD versus patients with type 1 diabetes alone, an increase in HbA1c of 8.3 ± 1.1 % to 8.9 ± 1.5 % was observed.10 As such, 91 evaluable individuals per group are required to provide 80 % power to detect a difference of at least 0.5 % at the 0.05 level of significance. The enrolment of 200 participants will allow for a non-evaluable rate of about 10 %. To reach the recruitment target of 200 individuals, approximately 5000 patients with an established diagnosis of type 1 diabetes will be screened for asymptomatic CD. Efficacy analyses will be performed on the intent-to-treat population consisting of all randomized participants.

The primary efficacy outcome, the change in HbA1c at 12 months, will be analyzed using an analysis of covariance (ANCOVA) model that includes adjustment for baseline HbA1c, age groups and investigative sites. Treatment effect will be quantified using the point estimate, the two-sided 95 % CI, and associated p value. Significant effect will be declared at the 5 % significance level.

Severe hypoglycemic episodes over time will be analyzed as Poisson counts using the generalized estimating equations approach to account for correlation among repeated measures within an individual. The QOL data over time will be analyzed by means of a linear mixed effects model including factors for treatment, investigative sites, age groups, and baseline QOL scores. BG variability and change in Z-score at the lumbar spine will be analyzed using the ANCOVA approach. The Statistical Analysis System (SAS) procedures GENMOD, MIXED and GLM in SAS V.9.2, will be used to perform the respective analyses.

Patient consent: Obtained.

Ethics Approval: Research Ethics Board Hospital for Sick Children, University of Toronto and at all recruitment sites.

The CD-DIET study data safety and monitoring board will perform regular reviews of collected safety and efficacy data. The protocol was peer reviewed by the JDRF.

## Discussion and dissemination

The CD-DIET study is a large scale clinical trial that will further contribute to the pool of knowledge and novel implications to the treatment of asymptomatic celiac disease and TID. The dietary curriculum will be coordinated across all centers by the main site dietitian, using standardized educational materials and a manual of operations. Both pediatric and adult patients will be randomized to a GFD or GCD. Adherence to the diets will be determined from the dietary interview, TTG-IgA blood tests and CDAT (GFD) and subjects’ self-report. CDAT is highly correlated with Standardized Dietician Evaluation (SDE) and even superior to TTG IgA serology with regards to GFD adherence [31]. The Canadian context to the study is important, as the 2013 Canadian Diabetes Association’s clinical practice guidelines suggests a targeted symptom based screening approach [33]. While the literature supports the implementation of a GFD in symptomatic CD and T1D patients, it is less clear as to the benefits for asymptomatic patients. Our curriculum was established in concurrence with the current literature and is designed to address a number of issues: the limited educational literature the challenges associated with dietary quality and adherence and the implicated social challenges of a GF lifestyle in addition to T1D and. Participants will be supported by dietitians throughout the study and subjects on the intervention group and later the control group will have to have access to ‘Your Guide to Well-being: Managing Celiac disease and Diabetes' a resource specifically designed to address the nutritional intricacies and related challenges of both conditions: CD and T1D.

The dietary quality of the GFD will be assessed through food records and interviews. The literature reports that GF equivalents tend to be lower in micronutrients and fibre, but higher in calories, fat and sodium [5, 13]. The participant’s diets will be evaluated for deficiencies and imbalances of macronutrients and micronutrients. We will assess the quantity and quality of carbohydrate intake using the glycemic index as well as glycemic load and calculate dietary gluten in our subject population. Dietary gluten quantification was previously demonstrated in Europe and applied to one of our smaller pilot studies with some limitations inherent to methodology and with the Canadian and American nutrient databases. We have described a method to help apply the Osborne calculation in North America [11] and plan to correlate adherence to gluten consumption and describe our population’s consumption patterns as it relates to CD and T1D.

Participants will also have the opportunity to report their adherence to the diet that they are randomized to through a ‘self-report’ questionnaire from ‘strict’ to ‘partial’ to ‘non’ adherent [34]. Although some studies show that patients overestimate adherence to GFD and that reliability of self-reports decreases with time on a GFD [16, 35], our previous findings show a close correlation between self-reports and dietitians’ assessment [36].

One of the greater challenges with asymptomatic patients if that they report better QOL and health prior to diagnosis [25]. This is likely due to the perceived burden of novel dietary restriction.

This study will answer some of the questions with regards to perceived benefits of GFD, especially when almost a third [37] of health practitioners are unsure whether they should be recommending GFD to asymptomatic patients [38]. The study was initiated in 2012, now active at 16 centers, and it is anticipated that results will be available by 2016.

